## Aims and Hypotheses

A feasibility study is underpowered to reliably assess treatment effectiveness (Williams, 2016). Therefore the primary focus of a feasibility study is not hypothesis testing, though statistical analysis of between-group outcome differences may be conducted in a preliminary way in order to inform the sample size calculations of future RCTs (Williams, 2016). Instead, as a feasibility study, the focus of this study is on collecting information that will support the design of future studies, e.g. recruitment rates, treatment adherence etc.

The primary aim of this study is therefore to examine whether it is possible to conduct an RCT with this population (mothers of new-born infants) and intervention (sling use, training and support). This study has a particular focus around the feasibility of recruitment of this population and also around treatment fidelity, including whether control group participants independently engage in sling use during the trial.

While this study is underpowered to draw definitive conclusions around treatment effectiveness, it is predicted that sling use will lead to lower Postnatal Depression scores (as measured by the Edinburgh Postnatal Depression Scale (Cox, Holden, & Sagovsky, 1987), and higher wellbeing scores (as measured by the Warwick Edinburgh Mental Wellbeing Scale (WEMWBS); Tennant et al., 2007), parenting self-efficacy and responsiveness (as measured by the Parenting Sense of Competency Scale (PSCS); Gibaud-Wallston & Wandersman, 1978; and Caregiving Experiences Questionnaire (CEQ); Brennan, George & Solomon, 2013), and breastfeeding frequency and duration, in the intervention group, compared to the control group. It is predicted that any improvement seen in the scores on these measures post-intervention, in comparison to pre-intervention scores, will be significantly greater for intervention group participants, than any improvement seen for control group participants.

A secondary hypothesis is that maternal attachment style (as measured by the Experiences in Close Relationships Scale-Short (ECR-S; Wei, Russell, Mallinckrodt & Vogel, 2007) might act as a moderator of the relationship between sling use and the scores on these various measures.

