### *Sample Size*

With regards to sample size, as this is a feasibility study and hypothesis testing is not the primary aim, a normal power calculation need not be undertaken (Eldridge et al., 2016; Williams, 2016). Instead the sample size should be selected based on whether it can adequately estimate parameters that will support the design of future RCTs, e.g. recruitment rates, treatment adherence, completion rates of outcome measures etc. Furthermore it is common for the sample size of a feasibility study to be influenced by practical considerations, such as demands on time and resources (Eldridge et al., 2016).

With these considerations in mind, and following the recommendations of the National Institute of Health Research (NIHR: Research Designs Service; Hooper, 2014), it was estimated that a sample size of 50-60 participants (25-30 per condition) is likely to be both feasible and able to accurately estimate parameters for future RCTs, such as drop-out rates and standard deviations which could be used to determine future sample sizes.

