### *Postnatal Depression*

Our primary measure is the Edinburgh Postnatal Depression Scale (EPDS; Cox, Holden & Sagovsky, 1987)(Appendix C) . The EPDS is a 10 item self-report scale designed to screen for postnatal depression in nonclinical populations. Participants give one of four possible responses to each of the ten statements. These possible responses indicate frequency, e.g. ranging from “Not at all” to “Yes, most of the time”, but the exact wording varies according to the statement. The scale typically takes around 5 minutes to complete (Cox et al., 1987).

The EPDS has been used widely in the National Health Service (NHS) as a screening tool for post-natal depression; and in previous studies in the field of maternal mental health and wellbeing (Leahy-Warren, McCarthy & Corcoran, 2012). A number of past studies found this scale to be a valid and reliable (Cox & Holden, 1994; Pope & Pope, 2000). In 2017, Cox published a 10 point supplement to their previous manual for this scale, designed to assist researchers in avoiding misuse of the EPDS (Cox, 2017). This study aims to follow both the manual for the scale (Cox, Holden & Henshaw, 2014), and this supplement (see Appendix D), in order to ensure standardised practice.

Because this measure is the primary screening tool for PND used in the NHS, if a participant scores above the clinical threshold implemented in the NHS, they will be sent a letter informing them of this, and encouraging them to access assessment and treatment for

postnatal depression via their GP or health visitor. This letter can be found in Appendix E.

At all three data collection time-points, information will be collected around whether participants are currently accessing pharmacotherapy or psychological care, using specific mental health-related items (please see Appendix B). This is in order to control for this variable during data analysis.

Recent studies have found that the sensitivity and specificity of the EPDS can vary between 59% to 100% and 44% to 97% (respectively) according to the geographic location of the study, the cutoff scores chosen by researchers, and the reference standards used for diagnosis (Novotney & Maurer, 2017).

Due to this variability in terms of sensitivity and specificity, some studies have recommended supplementing the EPDS with a second validated measure of depression that has shown less variation in sensitivity and specificity (Miller, Pallant, & Negri, 2006).

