### *Proposed Analysis*

As a feasibility study it is difficult to predict participant drop-out rate, and the impact that this may have on the results of the study. In order to control for drop-out, intention-to-treat (ITT) analysis will be used.

A mixed ANCOVA will be used to evaluate the relationship between sling provision and maternal mental health, wellbeing and parenting. This will include a comparison of both within-group pre- and post-intervention scores, and a between-group comparison of intervention vs. control group scores.

Attachment will be included as two covariates, as the measure of attachment used in this study produces two scores (*Avoidance* and *Anxiety*).

Thematic analysis will be used to evaluate the data collected from the two qualitative questions included at T3.

As a feasibility study, the impact of treatment fidelity on the results of the study is of interest. In order to examine this impact, it may be helpful to run the analysis again, this time excluding data from control participants who have used a sling, or accessed the sling surgery services over the course of the study. Similarly, it may be helpful to then re-run the analysis again, but this time excluding participants in the intervention condition who did not use their sling regularly. Through a similar process, it may be important to re-analyse the results of the study, investigating whether the frequency of participants' partners' sling use impacts upon these results.

It will be important to investigate whether the results of various demographic groups differ, in order to inform the inclusion or exclusion criteria of future RCTs. Frequencies and descriptive statistics derived from the demographic measures will be examined and presented. If possible, tests of difference will be conducted using this data, though this will of course depend upon the size of the demographic groups.

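### The planned mixed ANCOVA makes the T1 score part of the outcome and never a covariate, so the predicted treatment contrast is a change-score comparison with 1.18 to 1.54 times the variance of a T1-adjusted T3 comparison (assumed correlation 0.7 to 0.3)

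*Protocol*

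**What the plan says.** Proposed Analysis names the model: "A mixed ANCOVA will be used to evaluate the relationship between sling provision and maternal mental health, wellbeing and parenting". It then names two comparisons: one within each group, of scores before and after the intervention, and "a between-group comparison of intervention vs. control group scores". On covariates it says: "Attachment will be included as two covariates".

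One further adjustment variable appears elsewhere. Under Postnatal Depression in the Measures section, current drug or psychological treatment is recorded at every time point, and the stated reason is: "This is in order to control for this variable during data analysis". The T1 value of the outcome itself is not named as a covariate in either place.

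Aims and Hypotheses predicts lower depression scores and higher scores on the other measures than in the control group. It also predicts that any pre-to-post improvement "will be significantly greater for intervention group participants, than any improvement seen for control group participants". The same section says that between-group analysis may be done to inform the sample size of later trials. Sample Size lists parameters to be estimated for that purpose, "such as drop-out rates and standard deviations which could be used to determine future sample sizes", and sets the target at 25 to 30 per condition.

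Under Data Collection, the full battery except demographics is given at T1 and T3, and the EPDS also at T2.

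**The concern.** When pre- and post-intervention scores are the two levels of a within-subject factor, the model offers two terms that involve the arm. The group-by-time term is the between-arm difference in change. The group main effect is the between-arm difference in each woman's mean over T1 and T3. Neither uses T1 to predict T3, although the trial collects T1 on every scale that it repeats at T3.

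The change contrast subtracts the whole T1 score, whatever the correlation between T1 and T3, and so carries T1's noise into the estimate. The main effect averages a pre-intervention score with a follow-up score and so dilutes any effect. Proposed Analysis does not say which term is the treatment estimate.

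At stake is the precision of the one effect estimate that this small trial would pass on to a future RCT, and the risk that the wrong term of the model is read as that estimate.

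**Working it through.** **Inputs.** From the protocol: 1:1 allocation and 25 to 30 women per arm. There is no power calculation to reproduce, because the protocol declines one and states no alpha, effect size, SD or correlation. Assumed for illustration: unit SD at each time point, a T3 difference of 0.5 SD, two-sided 5%, and r = 0.3, 0.5 or 0.7. With the attachment scores in the model, r is read as the correlation given those scores.

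**Step 1: variances, with n per arm.**

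- Change contrast (group by time): (2/n) × 2(1 − r)
- T3 adjusted for T1: (2/n) × (1 − r²)
- Ratio: 2(1 − r) / [(1 − r)(1 + r)] = 2/(1 + r)

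The ratio exceeds 1 for every r below 1.

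| r | Variance ratio 2/(1+r) | SE ratio (square root) |
|---|---|---|
| 0.3 | 2/1.3 = 1.54 | 1.24 |
| 0.5 | 2/1.5 = 1.33 | 1.15 |
| 0.7 | 2/1.7 = 1.18 | 1.08 |

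Put another way, 30 per arm analysed as change is worth 30 × (1 + r)/2 = 19.5, 22.5 or 25.5 per arm analysed with T1 as covariate.

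**Step 2: standard errors (in SD units) and power for 0.5 SD (normal approximation).**

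| n per arm | r | SE, change | SE, T1-adjusted | Power, change | Power, T1-adjusted |
|---|---|---|---|---|---|
| 30 | 0.3 | 0.306 | 0.246 | 37% | 53% |
| 30 | 0.5 | 0.258 | 0.224 | 49% | 61% |
| 30 | 0.7 | 0.200 | 0.184 | 71% | 77% |
| 25 | 0.3 | 0.335 | 0.270 | 32% | 46% |
| 25 | 0.5 | 0.283 | 0.245 | 42% | 53% |
| 25 | 0.7 | 0.219 | 0.202 | 63% | 70% |

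With the noncentral t, the r = 0.5 pair at 30 per arm is 48% and 59%. For comparison, T3 alone, ignoring T1, has SE 0.258 at 30 per arm. Below r = 0.5 the change contrast is therefore less precise than not using T1 at all.

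**Step 3: the group main effect.** Over T1 and T3 its expectation is (0 + δ)/2 = δ/2, where δ is the T3 difference. For the EPDS over three time points it is:

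- (0 + 1 + 1)/3 = 0.67 of δ if the full effect is present at T2 and T3
- (0 + 0.5 + 1)/3 = 0.50 of δ if the effect grows linearly
- (0 + 0 + 1)/3 = 0.33 of δ if the effect appears only at T3

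**Step 4: simulation check.** In 20,000 simulated trials with 30 per arm, r = 0.5 and a true difference of 0.50, the mean estimates were 0.25 (main effect), 0.50 (change) and 0.50 (T1-adjusted). The empirical SEs of the last two were 0.259 and 0.225, in line with Step 2.

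**Step 5: what a later trial needs.** For 0.5 SD and 90% power (assumed), an unadjusted analysis needs 85 per arm. A T1-adjusted analysis needs 77, 64 or 43 per arm at r = 0.3, 0.5 or 0.7. Moving between these figures requires the correlation, which Sample Size does not list among its example outputs.

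**The case against.** Four points can be made for the plan as written.

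- **The effect is not halved.** A reader might infer from Step 3 that the trial will report half the true effect. The documents do not support that. Halving arises only if the group main effect averaged over T1 and T3 is reported as the treatment effect. Aims and Hypotheses states a prediction about improvement, and the debrief sheet (Appendix V) speaks of group differences and whether they change over time. Both point to the group-by-time contrast, which recovers the full effect. The between-group wording in Proposed Analysis could equally mean a comparison at T3. This objection stands. What remains is that the section lists that comparison without saying which term is the estimate.
- **The standard deviation is not wrong.** A reader might also infer that a future RCT would inherit the wrong SD. Sample Size neither specifies which SD is meant nor ties it to this model. The SD at each time point and the correlation can be estimated from the same data whatever model is fitted, and an unadjusted SD is a valid, conservative input. This stands too.
- **Detail may be left to an SAP.** The covariate list in Proposed Analysis is not exhaustive, as the mental-health treatment item shows, and an SAP may exist. This stands only in part. Placing pre-intervention scores inside the repeated outcome is a stated method, so the remedy replaces something the protocol says and does not merely fill a gap.
- **Feasibility aim.** Hypothesis testing is not the primary aim and no power target exists, so no stated figure is missed. That limits the weight of the point. It does not remove it, because the protocol gives informing later sample sizes as the reason for the between-group analysis.

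**Conclusion.** The point holds as a matter of precision. As planned, the predicted contrast is an unbiased change-score comparison with 18% to 54% more variance than T3 adjusted for T1, for r from 0.7 down to 0.3. That range is assumed; the direction holds for any r below 1. The group main effect over T1 and T3 is not suitable as the treatment estimate, but the protocol does not commit to using it as one.

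One assumption underlies both analyses. Under Procedure, women are randomised in pregnancy without blinding, and T1 follows when the infant is 0 to 6 weeks old. The adjusted and the change analysis alike therefore assume that allocation affects neither T1 scores nor T1 completion. The message templates in Appendix S give some support: the welcome email does not mention the arm, and the intervention group's invitation comes at the end of T1.

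The feasibility outcomes are untouched. This is a worthwhile, nearly free improvement to a preliminary analysis.

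**What to change.** In Proposed Analysis:

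- Name as the treatment estimate, for each scale measured at T1 and T3, the between-arm difference in T3 score with a confidence interval, adjusted for the same scale's T1 score alongside the two attachment scores.
- For the EPDS, model T2 and T3 as outcomes with T1 as covariate and an arm-by-time term.
- State that a group main effect averaged over T1 and follow-up is not the treatment estimate.
- State the assumption that allocation does not affect T1 scores or T1 completion, and report T1 completion by arm.

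In Sample Size, add to the listed outputs the SD at each time point and the T1–T3 correlation, each with a confidence interval, so that a later RCT can be sized for either an unadjusted or a baseline-adjusted analysis.

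The cost is a few sentences of wording. No new measure, visit or participant is required.

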## Abstract

Postnatal depression affects 10-15% of women worldwide (Cox, Murray, & Chapman, 1993). This randomised feasibility study investigates whether using an infant carrier leads to reductions in postnatal depression scores, increased wellbeing scores, and changes in parenting experiences. Maternal attachment style is examined as a potential moderator of this effect. Mothers of infants aged 0-6 weeks will be randomised to receive sling training and free sling hire, either immediately, or after a wait list period of 12 weeks (the control group). This study aims to collect information regarding the feasibility of recruitment and administering the intervention for future Randomized Control Trials.

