Parental “attachment style”, which refers to how the person approaches relationships later in life (Jones, Cassidy, & Shaver, 2015), may moderate the relationship between sling use and postnatal depression.

Parents with different attachment styles appear to differ in their thoughts and feelings about parenting (Millings, Walsh, Hepper, & O’Brien, 2013; Rholes, Simpson, & Friedman, 2006) and also about close physical contact (Posado, Waters, Crowell & Lay, 1995; Simpson, Rholes & Nelligan, 1992). Thus mothers with different attachment styles may respond differently to interventions for PND which involve such contact.

The aim of this study is to be the first to examine whether sling use may have a positive impact upon symptoms of postnatal depression, and furthermore, whether parental attachment style mediates this relationship.

Ideally, a randomised control trial (RCT) design would be used to establish a causal relationship between sling use and reduced occurrence of postnatal depression (Cartwright, 2010). To the researchers’ knowledge, there has not yet been an RCT that examines the impact of sling use on the parent specifically. However, before investing time and resources in a full-scale RCT, it is important to know whether it is possible to study the impact of this intervention (sling use) upon this population (mothers of young infants). In particular, it is anticipated that there may be challenges around recruitment and treatment fidelity.

For these reasons this study is a feasibility study, gathering information which may be used to estimate parameters (e.g. sample size, likely recruitment and drop-out rates) for future RCTs.

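### The secondary hypothesis is that attachment moderates the sling effect, but the analysis described enters attachment as covariates and names no interaction with group, so it gives no estimate of moderation

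*Protocol*

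**What the plan says.** The protocol gives attachment the role of moderator in three places:

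- Abstract: "Maternal attachment style is examined as a potential moderator of this effect".
- Introduction, closing paragraphs: attachment style "may moderate the relationship between sling use and postnatal depression".
- Aims and Hypotheses, where it is the secondary hypothesis: attachment "might act as a moderator of the relationship between sling use and the scores on these various measures".

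One sentence shortly after the second of these departs from the rest and gives as an aim to examine "whether parental attachment style mediates this relationship".

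The analysis is set out in Proposed Analysis: "A mixed ANCOVA will be used to evaluate the relationship between sling provision and maternal mental health, wellbeing and parenting". On the contrasts it adds: "This will include a comparison of both within-group pre- and post-intervention scores, and a between-group comparison of intervention vs. control group scores". On attachment it has one sentence: "Attachment will be included as two covariates, as the measure of attachment used in this study produces two scores", the two being Avoidance and Anxiety. The re-analyses listed there concern sling use among controls, low use in the intervention group, partners' use and demographic groups. None concerns attachment.

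Sample Size judges that "a sample size of 50-60 participants (25-30 per condition) is likely to be both feasible and able to accurately estimate parameters". Data Collection gives the attachment scale at baseline (T1) and repeats the full battery, apart from demographics, at T3.

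**The concern.** Moderation means that the sling effect differs between mothers with different attachment scores. Statistically it is an interaction between group and attachment. A covariate in an ANCOVA does another job: it removes the average association of attachment with the outcome and holds the treatment effect equal at every attachment score. An analyst who follows the described model therefore has no coefficient that answers the secondary hypothesis. The coefficient the model does provide, the attachment covariate, describes how attachment relates to mood or parenting in both groups together and carries no information on whether slings work differently.

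Mediation is a different question again and needs a different model, so the single use of that word leaves the intended role of attachment unclear.

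**Working it through.** The protocol gives no power, SD or effect size for this hypothesis, so there is no figure of its own to reproduce. The check has four steps.

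**1. What the described model contains.** Write G for group, and Anx and Avo for the two centred attachment scores. For a follow-up score adjusted for baseline:

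- As described: Y = b0 + b1 G + b2 baseline + b3 Anx + b4 Avo + error. The sling effect is b1 at every attachment score.
- With moderation: the same plus b5 G x Anx + b6 G x Avo. The sling effect is b1 + b5 Anx + b6 Avo.

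The secondary hypothesis concerns b5 and b6. The described model fixes both at zero.

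**2. The mixed form.** With time as a within-subject factor, the sling effect is group x time, so its moderation is group x time x attachment. Covariate x time terms, which some software adds by default, do not involve group and do not supply it. A group x attachment term alone is not enough either, because it averages over time points that include T1, before any sling is supplied. If moderation is 0 at T1 and d at T3, that term estimates (0 + d)/2 = d/2.

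**3. Precision once the terms are added.** Inputs: n = 50-60 (Sample Size) and 1:1 allocation (Procedure). Assumed, because the protocol does not give them: two-sided 5% level, one follow-up score adjusted for baseline, no dropout, uncorrelated Anxiety and Avoidance. The unit is the residual SD of the outcome per 1 SD of attachment.

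SE of one interaction coefficient = 2/sqrt(n); half-width = 1.96 x SE; slope difference detectable with 80% power = (1.96 + 0.84) x SE.

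| | n = 50 | n = 60 |
|---|---|---|
| SE | 0.283 | 0.258 |
| 95% half-width | 0.55 | 0.51 |
| Detectable at 80% power | 0.79 | 0.72 |
| Power for a slope difference of 0.5 | 42% | 49% |
| Power for a slope difference of 0.3 | 18% | 21% |

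Dropout reduces n, and correlation r between the two scores multiplies the SE by about 1/sqrt(1 - r^2). Both widen the interval.

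**4. Simulation of the two models.** 3000 runs per setting, a single follow-up score adjusted for baseline, no average sling effect, residual SD 0.8, and true moderation of 0, 0.3, 0.5 or 1.0 outcome units per SD of Anxiety (0, 0.375, 0.625 and 1.25 residual SD after division by 0.8).

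| True moderation (outcome units) | Joint 2-df interaction test rejects, n = 50 | n = 60 |
|---|---|---|
| 0 | 5% | 5% |
| 0.3 | 17% | 20% |
| 0.5 | 41% | 49% |
| 1.0 | 95% | 97% |

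In the covariate-only model the treatment test rejected in about 4-6% of runs at every level. Even large moderation leaves no trace there, as step 1 implies.

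**The case against.** The strongest reply is that Proposed Analysis is a short outline. It lists no model terms at all, not even group x time, and it does not say that attachment enters as main effects only. Interaction terms are often left to a statistical analysis plan, which may exist. This stands in part. A reader might infer that the protocol rules out any test of moderation, and the text does not go that far. But the protocol is not silent: it says how attachment enters the model, and that statement does not answer its own hypothesis. A later plan that followed it would inherit the mismatch.

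The second reply is that this is a feasibility study whose stated focus is not hypothesis testing, and that the hypothesis is secondary and tentatively worded. That stands, and it limits the weight of the point. A reader might infer that the trial's conclusions are at risk. Nothing on recruitment, fidelity or sling use among controls depends on this analysis. Nor does any text propose reading a significant attachment covariate as evidence of moderation; that is a possible misreading, not a planned one.

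Third, a reader might infer that attachment cannot be a mediator because it is measured before the sling is supplied. That is true only of the T1 score, since the scale is given again at T3. The better ground for treating the mediation sentence as a slip is that the Abstract, the Aims and the Introduction's own preceding text all speak of moderation.

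**Conclusion.** The point holds in limited form. The protocol states a moderation hypothesis and describes an analysis with no term for it, so the analysis as described would give no estimate of the secondary hypothesis. That conclusion follows from the form of the model and needs no numerical assumption.

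The precision figures do rest on assumptions: the half-width of 0.51-0.55 residual SD per SD of attachment is a best case under the conditions listed in the working. They show that the added terms can be estimated, but only imprecisely, so low power argues for an interval rather than a test and does not justify leaving the terms out. This should be fixed; it is not critical.

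**What to change.** In Proposed Analysis, replace the sentence on attachment with text to this effect:

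> T1 attachment Anxiety and Avoidance, continuous and mean-centred, enter the model. Where time is a within-subject factor, the model includes the group x time x attachment interactions and all their lower-order terms. Where a follow-up score is modelled adjusted for its baseline, it includes the group x attachment interactions. The interaction coefficients are reported with 95% confidence intervals as exploratory estimates of moderation, not as hypothesis tests.

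Naming T1 matters because the scale is repeated at T3, and only the T1 score precedes sling supply. In the Introduction, change the verb for the role of attachment from mediates to moderates.

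The cost is small and no new data are needed. The baseline-adjusted form adds two coefficients. The mixed form with two time points adds up to six: three for each of the two scores, namely group x attachment, time x attachment and the three-way term. The price is those degrees of freedom in a sample of 50-60, and wide intervals that must be labelled exploratory.
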